### Test battery for attentional performance (TAP)

The TAP is a computer-based test battery to assess attention [31]. We will use three different tasks from that battery to assess attentional control.

During the *Go/No-Go task*, participants will have to press a button whenever a go stimulus (i.e., a cross) will be shown on the screen. For no-go stimuli (i.e., a plus sign), a response needs to be inhibited.

During the *flexibility task*, a number and a letter are simultaneously presented left or right to a fixation cross. Participants will need to indicate the location of a target stimulus (i.e., either the number or the letter) with button presses. The target stimulus will alternate, beginning with the letter, then the number, then the letter and so on.

Finally, we will use a *dual task*. Participants will see different patterns of X’s on a grid. Whenever four X’s will build a square, the participants will need to press a button. Simultaneously, they will hear two alternating pitched tones. Whenever the same tone will be presented twice, the participants will need to press the same button.

For statistical analysis, we will calculate the number of false alarms during the Go/No-Go task, the number of correctly recognized targets during the flexibility task, and the number of missed targets during the dual task. For all three tasks, reaction times of correct answers will also be of primary interest. For secondary analyses, we will the intra-individual coefficient of variation (ICV), which examines attentional fluctuations [35].

### Laboratory prospective memory task

We will use an adapted version of an event-based prospective memory task [36] and will again present stimuli with PsychoPy3 (v2021.1.3). The paradigm will consist of an ongoing task as well as a prospective memory task (Fig 4). During the ongoing task, the participants will indicate by button presses whether a word pair belongs to the same semantic category or not. For the prospective memory task, they will additionally need to remember the colour and the letter of a string of letters that will appear instead of a word pair from time to time (i.e., ‘v’ or ‘c’). Whenever one of the subsequent word pairs will be presented in the same colour as the letter string, participants will need to press the respective letter key (e.g., ‘c’; Fig 4). That means, they would need to inhibit a response to the ongoing task (i.e., indicating whether the two words belong to the same category or not). The letter string represents a prospective memory intention that has to be retrieved when a specific event occurs (i.e., event-based prospective memory). At the end of the task, an ongoing-only block will be added. This block will include prospective memory cues that the participants will need to ignore. With the ongoing-only block, we will assess possible aftereffects of prospective memory (i.e., difficulties to inhibit prospective memory intentions). The task will consist of 178 word pairs and 12 letter strings. The ongoing-only block will consist of 38 word pairs, and three (irrelevant) prospective memory letter strings. For the generation of word pairs, we will use a list of 633 words, from which 216 words (belonging to 36 different categories) [37, 38] will be chosen randomly (i.e., half of these will be used for each session). There will be two lists of words (A or B). Each list will contain the same words, either paired with another word from the same category or not. Half of the participants will see list A in the first session and list B in the second and vice versa. The letter strings (i.e., ‘v’ or ‘c’) will be presented for 4 s, either in magenta or in green. The word pairs for ongoing trials will be shown for 3 s in red, blue, white, yellow, cyan, or orange. Between a letter string and a word pair with the corresponding font colour (i.e., magenta or green), 6 to 10 word pairs will be presented. All ongoing-task colour fonts, except orange and cyan, may appear several times between the presentation of two letter strings. Cyan and orange will be used with similar frequency as magenta and green (i.e., prospective memory cue). This will control for effects of low frequency of colours: Words displayed in cyan or orange should be identified as ongoing-task stimuli although they appear equally often as the prospective memory cue colours. Again, task instructions will be provided orally and in writing. The participants will train the task with different word pairs until two prospective memory intentions will be correctly identified. Again, the training will be done immediately before the actual task begins.

**Fig 4 pone.0289532.g004:**
[figure not shown]
Prospective memory task. As an ongoing task, participants will need to indicate via button press whether two words belong to the same category or not. In addition, when a letter string appears, they will need to memorize the letter as well as its font colour (in the example ‘c’ and ‘green’). Whenever one of the following word pairs will be presented in the same colour as the letter string (here: green), participants will need to press the respective letter key (here: ‘c’).

For statistical analysis, we will focus on prospective memory accuracy and reaction times. Modulating brain activity might also influence performance in the ongoing task. Therefore, we will evaluate as a secondary analysis the mean reaction time of correct ongoing task trials (i.e., as an indicator of ongoing task performance) as well as their ICV, as an indicator of attentional fluctuations [35, 39, 40].

### Prospective memory questionnaires

We will use two different questionnaires to assess self-reported prospective and retrospective memory failures. In the first session, we will use the *Prospective Retrospective Memory Questionnaire* (PRMQ) [41]. With this questionnaire, the participants will need to rate how often they experience memory failures (16 examples) on a scale from 1 = very often to 5 = never. Half of the items refer to retrospective memory, the other half to prospective memory failures in everyday life. In the second session, we will use the *Metacognitive Prospective Memory Questionnaire* (MPMI-s) [42]. With this questionnaire we will assess prospective-memory abilities as well as strategy use for prospective remembering. The participants will rate 24 statements on a scale ranging from 1 = rarely to 5 = often.

### Naturalistic prospective memory tasks

To assess naturalistic prospective memory, we will adapt the *Royal Prince Alfred Prospective Memory Task* [43]. The task consists of two prospective intentions that need to be remembered during the on-site session as well as two intentions that need to be remembered later at home. We will use two different versions of the task, one for each session (see Table 1). The order of the versions will be counterbalanced across participants. The participants will receive a score in each of these tasks depending on how timely and accurately the intention was retrieved (ranging from 0 = late and incorrect retrieval to 3 = correct and timely retrieval). Participants will be told not to use any external memory aids. The naturalistic tasks will be as follows: The participants will need to alert the experimenter after finishing a specific questionnaire and when five minutes have elapsed. In addition, they will need to leave a message on the study phone as soon as they arrive at home as well as five days after the session. The participants will have to repeat the instructions to guarantee correct understanding. The sum of all scores achieved in the naturalistic prospective memory tasks will be used for statistical analysis.

**Table 1 pone.0289532.t001:** Naturalistic prospective memory tasks used in our study.

	Version A	Version B

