### Statistical analysis

Our primary outcome measures will be performance in attentional control and laboratory prospective memory tasks: From the ANT, we will evaluate the controlling variable. From the TAP, we will use the number of false alarms in the Go/No-Go tasks, correct answers in the flexibility task, the number of missed targets in the dual task, and mean reaction times. For laboratory prospective memory, accuracy and reaction times will be evaluated. We will use mixed ANOVAs or mixed effects models for statistical analysis of stimulation effects on primary outcome variables (depending on whether there will be any missing data). In contrast to an ANOVA, mixed effects models are better capable of handling missing data and they also allow an analysis of data on a trial level while taking hierarchical structures of data and variability within subjects into account. We will use session (first, second) as within-subject factor and condition (six experimental groups or sham) as between-subject factor. We will determine whether inhibiting or enhancing activity in the left or right frontal inferior lobe or the right superior parietal lobe will modulate attentional control or prospective memory.

As secondary outcomes, we will evaluate accuracy of the ongoing task as well as ICV of reaction times during attentional control or the ongoing-task of the laboratory prospective memory paradigm. In addition, we will test whether stimulation will have any effect on alerting or orienting (i.e., ANT Task). We will then test whether attentional control significantly predicts laboratory, naturalistic, or self-reported prospective memory using multiple linear regression.

Further we plan to model laboratory prospective memory responses by using multinomial modelling of response probabilities [51]. This approach estimates both the prospective component (i.e., remembering *that* you have to do something) and the retrospective component (e.g., remembering *when* and *what* you have to do) of prospective memory.

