The results of our study will allow future perspectives for non-invasive brain stimulation research in the fields of prospective memory and attentional control in older adults. If attentional control or prospective memory can be enhanced with high-definition tDCS, its feasibility for long-term interventions may be evaluated in the future. A combination of cognitive training and repeated stimulation may, for instance, be promising. A recent meta-analysis by Jones and colleagues [59] found that a cognitive training with memory and/ or attention exercises can be useful for improving prospective memory. These effects may even be enhanced by non-invasive brain stimulation. As tDCS merely modulates brain activity that is already present (e.g., evoked by a task), the stimulation protocol may need to be personalized (e.g., using neuro-navigation) [60]. Compared to conventional tDCS, high-definition tDCS allows focal stimulation and also prevents bidirectional modulation within a brain area [61]. Therefore, predictions of stimulation effects on cognitive outcomes may be more precise and personalized stimulation may be more accurate. The transfer of training or stimulation effects from the laboratory to participants’ daily lives will be a big challenge for future interventions, though.

The results of our study, in particular the predictive value of attentional control for prospective memory, may contribute to this topic. Based on the integrative framework by Zuber and colleagues [2], we expect to find differences in the predictive value, depending on the ecological validity of the prospective memory task. The analysis of the predictive value may also contribute to a better understanding of the ‘age-prospective memory paradox’ which postulates that an impaired prospective memory in older adults is typically found in laboratory, but not in naturalistic tasks [62]. If we find evidence that attentional control is differentially predictive of naturalistic vs. laboratory tasks, this may contribute to the explanation of the paradox and may provide hints on how laboratory prospective memory tasks should be adapted to address similar functions as in naturalistic tasks.

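### Laboratory and naturalistic prospective memory are compared as outcomes of attentional control although the scores differ in length, so unequal reliability could by itself produce or exaggerate the hypothesised weaker naturalistic prediction

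*Protocol article*

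**What the plan says.** The Introduction states a directional hypothesis: attentional control should predict laboratory prospective memory, and not self-reported or naturalistic memory. Statistical analysis tests whether each of the three is significantly predicted, using multiple linear regression; it states no comparison between the coefficients. The Discussion adds that "we expect to find differences in the predictive value, depending on the ecological validity of the prospective memory task", and would carry a differential result over to the age-prospective memory paradox.

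The scores are built as follows.

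- **Laboratory task:** "The task will consist of 178 word pairs and 12 letter strings". The ongoing-only block adds three strings that participants must ignore, so these are not further opportunities for a hit. On the outcome: "For laboratory prospective memory, accuracy and reaction times will be evaluated".
- **Naturalistic task:** "The task consists of two prospective intentions that need to be remembered during the on-site session as well as two intentions" for later at home, hence four per session. They cross event-based with time-based cues and on-site with home settings, and one falls due five days later. Each is scored on a scale "ranging from 0 = late and incorrect retrieval to 3 = correct and timely retrieval". On repetition: "We will use two different versions of the task, one for each session". On the outcome: "The sum of all scores achieved in the naturalistic prospective memory tasks will be used for statistical analysis". Whether that sum covers one session or both is left open.

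**The concern.** Random error in an outcome multiplies its correlation with any predictor by the square root of the outcome's reliability, and reduces R² in proportion to that reliability. If items are of similar quality, a sum of four mixed tasks is less reliable than a score from 12 near-identical cues. Two constructs equally related to attentional control would then show unequal standardised coefficients and unequal chances of significance, in the direction the authors predict. A formal test of the raw coefficients would share this bias.

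At stake is one of the trial's stated hypotheses. A pattern of laboratory significant and naturalistic not significant could be taken as evidence about ecological validity when it partly or wholly reflects how long each test is.

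**Working it through.** The plan gives no reliability, correlation or power for this analysis, so there is no figure of its own to reproduce. Its sample size calculation concerns the seven-group ANOVA and does not bear on this point.

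**Inputs from the protocol article:** 12 laboratory cues and 4 naturalistic tasks per session, two sessions, n = 105, significance level 0.05 (two-sided assumed), age as one covariate.

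**Assumptions:** the same inter-item correlation r in both tasks, 0.10–0.25; true-score correlation with attentional control 0.40 for both outcomes; predictor reliability 0.6–0.8.

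**Step 1, reliability.** Spearman-Brown: rel = k·r / (1 + (k − 1)·r).

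| r | k = 4 | k = 8 | k = 12 | k = 24 |
|---|---|---|---|---|
| 0.10 | 0.31 | 0.47 | 0.57 | 0.73 |
| 0.15 | 0.41 | 0.59 | 0.68 | 0.81 |
| 0.20 | 0.50 | 0.67 | 0.75 | 0.86 |
| 0.25 | 0.57 | 0.73 | 0.80 | 0.89 |

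For example, at r = 0.10: 0.40/1.30 = 0.308 for four items and 1.20/2.10 = 0.571 for 12.

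**Step 2, attenuation.** Ratio of naturalistic to laboratory coefficient at equal true association = √(rel_nat / rel_lab).

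- 4 against 12: √(0.308/0.571) = 0.73 to √(0.571/0.800) = 0.85, so 15–27% smaller.
- 8 against 24 (both sessions on both sides): 0.80 to 0.90, so 10–20% smaller.
- 8 against 12: 0.91 to 0.95, so about 5–9% smaller.

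**Step 3, power, 4 against 12.** Observed correlation = 0.40·√(rel_x·rel_y); Fisher z with standard error 1/√(105 − 3 − 1) = 1/√101.

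- Low end (rel_x = 0.6, r = 0.10): laboratory 0.234, power 67%; naturalistic 0.172, power 41%.
- High end (rel_x = 0.8, r = 0.25): laboratory 0.320, power 92%; naturalistic 0.270, power 80%.

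**Step 4, discordant results, treating the tests as independent.**

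- Laboratory only: 0.669 × (1 − 0.415) = 39% at the low end, 0.915 × (1 − 0.796) = 19% at the high end.
- Naturalistic only: 0.415 × (1 − 0.669) = 14%, and 0.796 × (1 − 0.915) = 7%.

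**Step 5, simulation without the independence assumption.** One common ability, binary laboratory items, naturalistic items graded 0–3, n = 105, latent correlation 0.3 or 0.4.

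| Setting (item r, naturalistic / laboratory) | Laboratory only | Naturalistic only |
|---|---|---|
| 4 against 12, equal r of 0.2 or 0.3 | 11–24% | 3–10% |
| 4 against 12, 0.15 / 0.30 | 30–35% | 2–5% |
| 4 against 12, 0.4 / 0.2 | 5–11% | 6–13% |
| 4 against 12, 0.5 / 0.2 | 3–9% | 7–15% |
| 8 against 12, equal r of 0.2 or 0.3 | 4–14% | 3–12% |

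In the first setting the naturalistic correlation was the smaller in 65–72% of trials.

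**Step 6, break-even.** Setting the reliabilities equal, the four-item score needs an inter-item correlation of rel_12 / (4 − 3·rel_12): 0.25 when the laboratory value is 0.10, and 0.43 when it is 0.20.

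**The case against.** A reader might infer that unequal reliability alone will produce the hypothesised result. The documents do not support that. They give no reliability or inter-item correlation for either score, so the inequality is inferred from item counts plus an assumption. Several features could narrow or remove it:

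- Naturalistic tasks are graded 0–3, which recovers information that a right-or-wrong cue loses.
- The sum may cover eight tasks. Against 12 binary cues at equal item correlation, the simulated gap all but disappears.
- If naturalistic tasks intercorrelate much more strongly than laboratory cues, the gap reverses.
- Laboratory memory is also analysed by reaction time, to which a cue count does not transfer directly.

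Length also cannot explain the self-report part of the hypothesis, since the questionnaires have 16 and 24 items. The authors give a substantive reason for their prediction too: laboratory tasks share a setting and need prompt motor responses. The independence calculation overstates discordance, because both regressions use the same people and predictor, and the reverse pattern must be counted as well.

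The analysis lies outside the primary outcomes, the paradox remark is conditional, and reliability reporting could sit in an analysis plan that is not shown.

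All this limits the claim to a possible bias. It does not remove it: each caveat shows that the unknown relative reliability can decide the answer. What the article does state is the separate significance tests and the reading of a difference as ecological validity.

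**Conclusion.** The concern holds as a possibility, not as a certain result. With equal true associations, the stated approach can favour the authors' hypothesis through score length. On the four-against-12 reading, the expected loss in the naturalistic coefficient is 15–27%, and laboratory-only significance is more frequent than the reverse: 19–39% against 7–14% under independence, 11–24% against 3–10% in the simulation with equal item correlations.

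These figures rest on the assumed inter-item correlations, a true correlation of 0.3–0.4, all 105 participants being analysed and, in the first calculation, a predictor reliability of 0.6–0.8. Less homogeneous naturalistic tasks, which their mixed design makes plausible, would widen the gap; summing both sessions or stronger intercorrelation would shrink or reverse it. The point touches a secondary analysis, but one that tests a stated hypothesis and supports a main interpretation in the Discussion. It should be addressed there and does not affect the primary stimulation comparisons.

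**What to change.** Do not infer laboratory rather than naturalistic prediction from separate significance tests. Instead:

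1. State whether the naturalistic sum covers one session or both.
2. Test the difference between the standardised coefficients directly, respecting that both come from the same participants.
3. Estimate each score's reliability from its session-1/session-2 correlation, adjusted for condition and for task version or word list. Note that session 2 includes stimulation, so individual differences in response to it also lower this correlation, and adjusting for condition removes only group means.
4. Show attenuation-corrected coefficients and their difference, with bootstrap intervals, beside the raw ones.
5. Attribute a difference to ecological validity only if the corrected results support it; otherwise state that unequal reliability may explain it.

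No new data are needed, since both tasks are run in both sessions. The cost is extra analysis and wide intervals for the naturalistic coefficient.

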**Short-term, event-based:**		
Between filling in the two questionnaires, please tell the experimenter…	to open the door to let some air in.	to get a new bottle of hand disinfectant.
**Short-term, time-based:**		
When five minutes have elapsed on the stopwatch, please tell the experimenter…	what you had for breakfast.	where you spent your last holiday.
**Long-term, event-based:**		
When you get home, please leave a message on the study phone about…	whether you are planning to watch TV this evening.	what you are planning to cook for dinner.
**Long-term, time-based:**		
In five days, please leave a message on the study phone about…	what the weather is like at your place.	what you are planning to do on this day.

### Heart rate

The participants will put on a wearable device (Polar Verity Sense by Polar Electro Europe AG, polar.ch) to their left arm with an elastic strap to monitor their heart rate. The device measures beats per minute for every second. Data will be saved on an internal memory during monitoring and will later be transferred to a computer. For statistical analysis we will use data assessed two minutes before the first task until two minutes after the prospective memory task (i.e., 24 min in total). Mean beats per minute within the first two minutes will serve as a baseline for each individual and will be used to standardize measurements of the following 22 minutes by subtracting the baseline from each of the following data points [44]. We will mainly assess the heart rate to control for a possible influence of agitation on cognition.

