### Study procedure

All participants will be tested twice to differentiate learning effects from stimulation effects (Fig 2). All assessments will be done by the same examiners (NS, RM) at the University Hospital of Old Age Psychiatry and Psychotherapy at the University of Bern, Switzerland. On the first day of the experiment, we will test verbal intelligence [27], followed by an assessment of current mood (Profile of Mood States, POMS; Positive and Negative Affect Scale, PANAS) [28–30]. Then, the participants will put on a wearable device (Polar Verity Sense by Polar Electro Europe AG, polar.ch) on their left arm that will monitor their heart rate. Next, they will be asked about how many hours they had slept the night before and how awake and motivated they currently feel. Then, the attention network task and the prospective memory task will follow. Next, they will do a Go/No-Go task, a flexibility task, and a divided attention task (TAP) [31]. Finally, they will again rate their current mood and different naturalistic prospective memory tasks will follow. The second day of the experiment will be identical with the exceptions that we will apply stimulation for 20 min during the attention network task and the prospective memory task and that there will be no verbal intelligence test. At the end of the experiment, side effects, and the participants’ perception of the stimulation condition will be captured [32].

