We will include age as a covariate in all models since it significantly influenced prospective memory in our previous study [52]. We will control for any potential influence of mood or agitation on cognition and test, in an exploratory analysis, whether mood or heart rate of participants will influence attentional control or prospective memory. Further we examine, whether one of these two measures are modulated by non-invasive brain stimulation. For an assessment of heart rate, we will include changes in beats per minute (relative to baseline) between the start of stimulation until two minutes after its end (i.e., 22 minutes). Generalized estimated equations will then be used to test any longitudinal stimulation effects on heart rate during the stimulation session [53–55].

We will use R (version 4.2.1) with RStudio (version 2022.02.3) for statistical analyses with *p* < 0.05 considered statistically significant. We will correct for multiple-comparisons using Bonferroni-Holm correction. Whenever the assumptions of normality and homogeneity are not met, data will be transformed and/or non-parametric alternatives will be used. We will only analyse data of participants that attended both sessions.

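### The analysed heart-rate window closes before the TAP, so agitation for six of the nine primary outcomes can only be represented by a proxy from earlier tasks

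*Protocol article*

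**What the plan says.** The Heart rate section of the protocol article fixes the data to be analysed: "we will use data assessed two minutes before the first task until two minutes after the prospective memory task", a span that it puts at 24 minutes. The first two minutes are the individual baseline, which is subtracted from every later data point. The same section gives the purpose: "We will mainly assess the heart rate to control for a possible influence of agitation on cognition". The Introduction likewise names mood ratings and heart rate as the means of controlling for mood and agitation.

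The Study procedure section sets the task order. After the preparatory questions, "Then, the attention network task and the prospective memory task will follow"; and then, "Next, they will do a Go/No-Go task, a flexibility task, and a divided attention task (TAP"). The second day follows the same order, except that there is no vocabulary test and "we will apply stimulation for 20 min during the attention network task and the prospective memory task". Mood is rated before the tasks and again after the TAP.

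The TAP section describes its three tasks as measures of attentional control and gives their reaction times primary interest. The Statistical analysis section lists the TAP counts and mean reaction times among the primary outcomes. It also states that mood and agitation will be controlled for, and that an exploratory analysis will test "whether mood or heart rate of participants will influence attentional control or prospective memory". For the assessment of heart rate it takes changes from baseline "between the start of stimulation until two minutes after its end (i.e., 22 minutes"), and it then names generalised estimating equations (GEE) for stimulation effects on heart rate.

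**The concern.** One window serves two purposes. It suits the question whether stimulation changes heart rate, because it spans the stimulation and a short tail. It does not suit the purpose that the article calls the main one, which is to account for agitation when cognition is measured. Most attentional-control outcomes come from the TAP, and the TAP is run after the window has closed.

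If heart rate from the earlier tasks stands in for heart rate during the TAP, it is an imperfect proxy to the extent that agitation changes between the two periods. Adjustment would then be incomplete, and an association between agitation and a TAP outcome would tend to look weaker than it is. A null result could be read as showing that agitation plays no role, when agitation was not measured at the relevant time. The window is stated explicitly, so this is a fixed choice and not a detail left to another document.

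**Working it through.** **1. Reproducing the plan's window.** Inputs: two-minute baseline and two-minute tail (Heart rate), 20 minutes of stimulation during the ANT and the prospective memory task (Study procedure).
- Whole window: 2 + 20 + 2 = 24 min, as stated in Heart rate.
- After baseline: 20 + 2 = 22 min, as stated in Statistical analysis.

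The two sections agree with each other. The figures imply that the ANT and the prospective memory task together fill about 20 minutes.

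**2. Is there room for the TAP inside those 20 minutes?**
- Prospective memory task: 178 word pairs × 3 s + 12 letter strings × 4 s = 534 + 48 = 582 s = 9.7 min.
- Ongoing-only block, if additional: 38 × 3 s + 3 × 4 s = 114 + 12 = 126 s = 2.1 min, giving 9.7 + 2.1 = 11.8 min.
- ANT: 144 trials. The trial length is not stated. At an assumed 3 to 5 s it takes 432 to 720 s, or 7.2 to 12.0 min.
- Sum: from 9.7 + 7.2 = 16.9 min to 11.8 + 12.0 = 23.8 min, before any time for training between the tasks.

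The two tasks roughly fill the period. In any case the Heart rate section ties the end of the window to the prospective memory task, and the TAP starts only after that task.

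**3. Counting the primary outcomes** (Statistical analysis, with the TAP section for the reaction times).
- ANT: controlling variable = 1.
- TAP: Go/No-Go false alarms, flexibility correct answers, dual-task misses = 3; reaction time in each of the three tasks = 3; together 6.
- Laboratory prospective memory: accuracy and reaction time = 2.
- Total: 1 + 6 + 2 = 9, of which 6 fall after the window.

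If mean reaction times are counted once, the TAP gives 3 + 1 = 4 and the total is 1 + 4 + 2 = 7, so 4 of 7. The TAP section names reaction times for all three tasks, which favours the count of 6 of 9.

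**4. What the tail can cover.** The article gives no interval between the prospective memory task and Go/No-Go. The two-minute tail may therefore overlap the start of Go/No-Go, but it is not defined as a TAP measure and it cannot be relied on for the later flexibility and dual tasks.

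**The case against.** The strongest reply is that nothing here contradicts itself. The window is consistent across sections and matches the stimulation period. The test of influence is labelled exploratory, and no treatment comparison depends on it. If agitation is a state that lasts through a session, heart rate from some minutes earlier is a reasonable proxy. It also precedes the TAP outcome, which suits a question about influence, whereas heart rate during a task may partly reflect effort on that task. All of this stands, and it keeps the point small. It does not remove the mismatch between the stated main purpose and the data kept for it.

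Several stronger readings are tempting, but the document does not support them:
- **That the ANT is related to heart rate recorded after it.** The article does not define a single 22-minute summary as the predictor for every outcome. Data are logged every second and each point is baseline-corrected, so an ANT-only summary is available from the planned data.
- **That no heart-rate data exist for the TAP.** The restriction is on the data analysed. The article does not say when the armband comes off.
- **That the TAP has no measure of state at all.** Mood and affect are rated before the tasks and again after the TAP.
- **That a definite amount of power is lost.** An assumed true correlation of 0.30, multiplied by an assumed correlation of 0.5 to 0.8 between the two periods, gives 0.15 to 0.24. None of these inputs is in the document, and the product assumes that agitation acts only through heart rate at the time of the TAP. It illustrates the direction and nothing more.

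**Conclusion.** The point holds as a minor design weakness. The analysed heart-rate window ends before the TAP, apart from a possible short overlap with Go/No-Go, while the plan promises an agitation analysis for attentional control that includes the TAP. Six of the nine primary outcomes are affected, or four of seven on the narrower count. For these, the stated agitation measure can only be a proxy from earlier tasks.

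This rests on the task order in Study procedure and on reading the window in Heart rate as applying to all uses of heart rate, since no other window is given for the agitation question. How much the proxy loses cannot be derived from the document. A reader might infer that the estimates of stimulation effects are compromised. They are not: the consequence is confined to the agitation covariate and the exploratory analysis, and the randomised comparison is not invalidated.

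**What to change.** In the Heart rate section, extend the retained data to the end of the dual task, and extend the recording as well if the armband is at present removed earlier. Derive a baseline-corrected mean heart rate separately for the ANT, the prospective memory task and each TAP task. In the agitation analysis under Statistical analysis, relate each outcome to heart rate from its own task period. Leave the 22-minute window for the GEE analysis of stimulation effects as it is. If recordings during the TAP cannot be obtained for some participants, state that heart rate for their TAP outcomes is a proxy from the earlier tasks.

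The cost is possibly longer wear of a device already in place and a few extra derived variables. The one scientific drawback is that heart rate within a task may partly reflect effort, so an association should be interpreted with that in mind.
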